### Population

The population comprises adults aged between 25 and 70 years living in households within the Cape Coast metropolis. The choice of this age range was influenced by the fact that they are at a higher risk of developing diabetes in the metropolis (41, 42). It is estimated that the number of people between the ages of 25 and 70 living in the Cape Coast Metropolis is 102,533 (43), spread across several households and communities in the metropolis. The sample for the study is being drawn from rural, peri-urban, and urban communities in the Cape Coast Metropolis. Owing to the heterogeneous nature of the Cape Coast population, the selection of participants for this study is based on different characteristics. These characteristics includes the type of community (rural, peri-urban, urban), main economic activity (farming, fishing, trading, formal work), dominant religion (Christianity, Islam, African traditional religion), and ethnicity (Fante, Ewe, Asante, northern tribes).

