### Participants

Following the protocol of the Research on Obesity and Diabetes among African Migrants (RODAM) study, which focused on obesity and type 2 diabetes among African migrants (44), this study estimates the prevalence of undiagnosed type 2 diabetes (T2D) in the Cape Coast metropolis of Ghana, at 6-7%, and the prevalence of obesity at 17%. The study aims for a power of 0.90 with α=0.05, including the Bonferroni correction. Using these parameters, a sample size of approximately 1000 would be sufficient to detect a 10% proportion of undiagnosed T2D. In order to compensate for attrition, the study seeks to recruit 1200 self-identified healthy individuals from 13 urban and rural communities in the Cape Coast Metropolis, who have not been previously diagnosed of diabetes or prediabetes prior to the study for collection of baseline data.

Due to the large and geographically dispersed population, a multistage sampling technique would be employed to sample participants for this study. This will be done in three stages, where the first stage involves dividing the population into clusters, based on the already existing communities within the metropolis. The second stage involves sampling these clusters to be used in the study by using systematic random sampling. At this stage, 13 clusters representing 13 rural, peri-urban and urban communities would be selected for the subsequent sampling stage. Finally, the third stage would involve further sampling within each selected cluster to randomly select households, and recruit the first two persons from each family line (with random replacement) in the indigenous communities, while using convenience sampling in non-indigenous communities. It is envisaged that approximately 90-100 participants will be randomly selected from three rural communities (Efutu Mampong, and Efutu), four fishing communities (Abekam, Duakor, Ekon, and Ntsen), three peri-urban communities (Ayeko-Ayeko, Ankaful and Nkanfoa) and one urban community (UCC), two market communities (Kotokuraba and Abura Markets), and one artisanal community (Siwdu). Household mapping will be done utilizing the 2021 Housing Census Data. All the 1200 volunteers will be recruited from their communities of origin before disclosing any monetary benefits.

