### Data analysis

For the accuracy of data and information, data collected through the Kobo Collect toolbox application will be downloaded into an Excel spreadsheet and screened visually and statistically. Data will be analyzed and interpreted by the principal investigator and his local collaborators and shared back with foreign collaborators. In the attempt to make the findings of the study public, data analysis will be conducted using STATA 16 and SPSS 23. Statistical tools specific and relevant to the research questions and hypotheses of the CarMeR study would be used. To determine the prevalence of undiagnosed diabetes, prediabetes and other associated cardiovascular risks, data on OGTT, FPG and HbA1c will be analyzed using descriptive statistics (percentages and confidence intervals). In order to investigate the differences in phenotype, diabetes, prediabetes, and normoglycemic groups will be compared based on BMI and body composition (waist hip ratio, body fat percentage, skeletal muscle, total body water) using analysis of variance (ANOVA) and t-test. To profile the ocular characteristics and complications of the diabetes and prediabetes groups, a cross-tabulation and a subsequent chi-square test will be done to assess the association between glycemic dysregulation and the presence of ocular complications (diabetic retinopathy, cataract, macular edema). For the purpose of ascertaining whether the predominant etiological factor of undiagnosed diabetes in this populations is insulin resistance or beta-cell failure, a homeostasis model analysis of beta [HOMA-β and HOMA-IR] will be computed and logistic regression will be used to determine the dominant factor. As a way of determining the sensitivity of other diagnostic alternatives (FPG and HbA1c) in comparison to the multi-sampled OGTT, receiver-operated characteristics (ROC curves), including sensitivity and specificity curves, will be used. Finally, to ascertain whether lifestyle changes (food choice, physical activity, weight loss, psychosocial counseling) over a one-year period impacts biomarkers of glucose regulation, a linear mixed model regression analysis, controlled for baseline characteristics will be used. T-tests will be conducted to observe changes in glucose regulation biomarkers.

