### Expected outcomes

The CarMeR study is expected to help provide insights on the burden and possible management of diabetes, prediabetes and related cardiometabolic complications in a typical African population. It will ascertain the prevalence of undiagnosed diabetes and prediabetes, as well as explore the relationship between these diseases and cardiovascular risks such as obesity, dietary habits, socioeconomic status, stress, sleep pattern and location. Furthermore, it will provide a nuanced understanding of the phenotypic and biochemical characteristics of the people with diabetes and prediabetes, with a focus on body composition, insulin resistance, and beta-cell function. The study will also describe the ocular characteristics of the participants, in order to identify the ocular complications associated with abnormal glucose tolerance. In the subsequent phase of the study, the efficacy of lifestyle interventions like diet, physical activity, and psychosocial counseling in preventing or reversing diabetes and prediabetes, will be assessed.

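### Near-equal takes from named communities, with no size-proportional selection stated and convenience sampling in some, mean the pooled percentage need not estimate prevalence in the metropolis

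*Protocol article*

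**What the plan says.** **Target.** The Population section of the protocol article defines the population as "adults aged between 25 and 70 years living in households within the Cape Coast metropolis" and puts it at 102,533 people. It gives no split by community or by urban and rural residence. Prevalence is the first of the six objectives at the end of the Introduction.

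**Selection of communities.** The Participants section describes three stages. On the second it says "The second stage involves sampling these clusters to be used in the study by using systematic random sampling", and then "At this stage, 13 clusters representing 13 rural, peri-urban and urban communities would be selected for the subsequent sampling stage". No measure of size enters the draw. The same paragraph already names the communities, grouped by type or main activity: "It is envisaged that approximately 90-100 participants will be randomly selected from three rural communities (Efutu Mampong, and Efutu", then four fishing and three peri-urban communities, "and one urban community (UCC), two market communities (Kotokuraba and Abura Markets), and one artisanal community (Siwdu". The Population section adds that selection rests on community type, economic activity, religion and ethnicity.

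**Selection within communities.** Households are chosen at random in indigenous communities, "while using convenience sampling in non-indigenous communities".

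**Analysis.** Under Data analysis, the OGTT, FPG and HbA1c data for prevalence "will be analyzed using descriptive statistics (percentages and confidence intervals". No weights are mentioned.

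**Location.** Expected outcomes lists it among the factors to be explored: "cardiovascular risks such as obesity, dietary habits, socioeconomic status, stress, sleep pattern and location". No objective and no stated test compares urban with rural residents.

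**The concern.** A prevalence for the metropolis is an average over its residents. A pooled percentage from near-equal takes is an average over communities. The two agree if communities were drawn with probability proportional to size, or if prevalence does not vary with community type and size. The plan states neither, and it treats location as a possible risk factor. A larger sample would not remove such a bias.

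Two features add to this. Convenience sampling leaves the chance of selection unknown in some communities. And the only community labelled urban is the university, so UCC set against the rest would mix urban residence with one institution, with no second urban cluster to show variation between communities.

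The description of the sample also disagrees with itself: in the number of communities, in the number of rural names, and in whether the communities are the result of a random draw or were chosen by type.

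**Working it through.** **Inputs from the protocol article:** 1200 recruits; 13 communities; about 90-100 participants; type counts 3 rural, 4 fishing, 3 peri-urban, 1 urban, 2 market, 1 artisanal (Participants); 102,533 residents aged 25-70 (Population).

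**Step 1: the plan's total.** The 90-100 must be per community, since no other reading gives 1200.
- 13 communities: 13 × 90 = 1170 and 13 × 100 = 1300; 1200/13 = 92.3. The stated total is reproduced.
- 14 communities: 14 × 90 = 1260 and 14 × 100 = 1400; 1200/14 = 85.7. It is not.

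**Step 2: the list.** The counts give 3 + 4 + 3 + 1 + 2 + 1 = 14. The printed names number 2 + 4 + 3 + 1 + 2 + 1 = 13, because only two names follow the three rural communities. The names fit the total; the counts do not.

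**Step 3: what equal takes imply.** Let a community have M residents aged 25-70, let the frame hold K communities, and let n ≈ 92 be taken from each of 13.
- Equal-probability draw of communities: a resident's chance is (13/K) × (n/M). A community ten times as large gives each resident one tenth of the chance, so an unweighted percentage over-represents small communities.
- Draw proportional to size: the chance is (13 × M/102,533) × (n/M) = 13n/102,533 ≈ 1200/102,533 = 1.17% for everyone. The sample is self-weighting.
- Convenience sampling within a community: the chance is undefined under either draw.

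**Step 4: possible size of the bias (illustration).** Let s be the urban share of the sample, W the urban share of residents, and p_U and p_O the prevalence in urban and other areas. Then bias = (s − W)(p_U − p_O). W and both prevalences are assumptions. UCC alone gives s = 1/13 = 0.077; adding the market and artisanal sites gives s = 4/13 = 0.308.

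| Assumed p_U, p_O | s | Sample estimate | True value, W = 0.30 to 0.80 | Bias (points) |
|---|---|---|---|---|
| 10%, 6.5% | 1/13 | 6.8% | 7.6% to 9.3% | −0.8 to −2.5 |
| 10%, 6.5% | 4/13 | 7.6% | 7.6% to 9.3% | 0.0 to −1.7 |
| 9%, 5% | 1/13 | 5.3% | 6.2% to 8.2% | −0.9 to −2.9 |
| 9%, 5% | 4/13 | 6.2% | 6.2% to 8.2% | 0.0 to −2.0 |

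With p_U = p_O the bias is zero; with p_O above p_U its sign reverses. For scale, a simple-random 95% half-width at 6.5% with n = 1200 is 1.96 × √(0.065 × 0.935/1200) = 1.4 points.

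**Step 5: price of weighting.** Variance factor = W²/s + (1 − W)²/(1 − s), with W = 0.60 assumed.
- Four urban sites of 14: 0.36/0.286 + 0.16/0.714 = 1.48; √1.48 = 1.22. Four of 13 gives 1.40 and 1.18. The interval is about 20% wider.
- UCC alone, 1 of 14: 0.36/0.0714 + 0.16/0.9286 = 5.2; √5.2 = 2.3. One of 13 gives 4.9 and 2.2. The interval is more than twice as wide.

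These factors leave out clustering within communities.

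**The case against.** A reader might infer that the communities were picked by hand and that the study can give neither a metropolis prevalence nor an urban-rural contrast. The documents do not support so much.

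- **Systematic random sampling is stated.** The named communities may be the result of that draw. Naming them by type, and the remark about selection on characteristics, point the other way. The text does not settle it.
- **Equal takes are not an error in themselves.** After a size-proportional draw they are self-weighting. That draw is not excluded; it is only not stated.
- **Weights may be set out elsewhere.** The article condenses a fuller plan, so silence on weights alone would be no finding. What remains is that the article fixes the allocation and the convenience sampling, and that weighting by residence needs home community recorded at recruitment.
- **No urban-rural comparison is planned.** This stands. The point about UCC applies only if location is explored.
- **One urban label does not mean one urban site.** Market and artisanal communities are labelled by activity and may well be urban.
- **Non-resident traders are conjecture.** Participants says volunteers come from their communities of origin. Still, the Questionnaire section recruits at markets, churches and schools, and the Inclusion criteria do not list metropolis residence.
- **The bias rests on assumed figures.** This stands too: it may be negligible, or run the other way.

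**Conclusion.** The point holds in limited form. As described, the sample yields an average over the selected communities. It estimates prevalence among metropolis household residents aged 25-70 only if communities were drawn in proportion to size or prevalence does not vary with community type and size, and if convenience selection does no harm. The plan secures none of these.

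Neither the size nor the direction of the bias can be determined from the documents. Under the assumed urban shares and gradients above, it runs from nil to almost 3 points low, against a simple-random half-width of 1.4 points. That shows what could be at stake and is not an estimate.

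The mismatch between 14 by count and 13 by name and statement is certain but changes no estimate. The unclear account of how the communities were chosen matters more, because it decides whether the percentages need weights.

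**What to change.** 1. Record each participant's home community at recruitment. Classify location by residence, and leave non-residents of the metropolis out of the prevalence estimate.
2. Report a prevalence weighted to census shares of residents aged 25-70 by community type, beside the unweighted figure. Group UCC, market and artisanal residents as urban where their residence supports it. The study already uses 2021 census data for household mapping; whether these give the needed shares has to be checked. State that weights do not correct convenience selection within communities. If shares are unavailable, describe the result as prevalence in the selected communities.
3. If location is explored, do not present UCC against the rest as an urban effect, and label any contrast descriptive.
4. Reconcile the community count, the rural names and the cluster-selection wording. State whether the named communities came from the systematic draw, and with what probabilities.

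**Cost.** One residence question, a census tabulation and weighted percentages, with no extra participants. The price is precision: with an assumed 60% of residents urban, the interval is about 20% wider if four sites supply the urban sample, and more than twice as wide if UCC alone does. In the second case the whole urban estimate would also rest on the university community, which is a further reason to group by residence.

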#### Inclusion criteria

Participants would be included in the study if they aged 25 to 70 years, and have not been diagnosed with prediabetes or diabetes. Additionally, participants should be willing to undergo the screening procedure (glucose testing, eye examination, BMI assessment, lipid level measurement, and body composition analysis). Participants diagnosed of diabetes based on a 2-hour OGTT glucose level between 11.1-17.0mml/L (200-300mg/dL) or prediabetes with 2-hour OGTT glucose level between 7.8-11.0 mmol/L (140-199mg/dL), would be followed up with a non-pharmacological lifestyle intervention for one year to assess the effect on their glucose tolerance.

#### Exclusion criteria

Pregnant or breastfeeding women, individuals with pre-existing diabetes (either type 1 or type 2), those with a BMI below 18.5 kg/m², individuals with anemia, and those on cholesterol medications will be excluded from the CarMeR study. These exclusion criteria have been carefully selected to align with the study’s primary objective of ascertaining the prevalence of undiagnosed diabetes within a target population. Pregnant women are excluded due to the possibility of abnormal glucose tolerance precipitated by the pregnancy, and the return to normal glucose tolerance postpartum. Individuals with pre-existing diabetes are excluded to maintain the study’s focus on detecting previously undiagnosed cases, and the exclusion of participants taking high cholesterol medications is a measure taken to address the potential confounding impact of elevated cholesterol levels on diabetes prevalence. In addition, lactating mothers and individuals diagnosed with anemia are excluded because of the blood sample collection. Such participants may be at an increased risk of adverse effects or discomfort associated with the blood drawing process. The exclusion of these categories of people was intended to prioritize participant well-being, conform to the tenets of the Declaration of Helsinki for research on human subjects, and ensure the integrity of the study and the accuracy of its findings.

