## Introduction

Research has established that obesity, high levels of glucose, and triglycerides are significant contributors to the risks of developing cardiometabolic diseases [CMDs] (1–4). However, literature suggests that two-thirds of African-born individuals in sub-Saharan Africa living in America diagnosed with abnormal glucose tolerance are more likely to be non-obese (5). This has led to research to establish the specific causes of diabetes and prediabetes in an African population, and to identify risk factors unique to Africans. The main mechanisms for the development of diabetes are beta-cell failure and insulin resistance, with abnormal glucose tolerance representing an imbalance between the degree of insulin resistance and the β-cell secretion (6–8). Identifying the etiology of diabetes is critical for prescribing the relevant treatment or interventions (6).

Globally, 537 million adults live with diabetes, with Africa contributing 4.47% (24 million) and witnessing 416,000 diabetes-related deaths in 2021 alone (9). According to the International Diabetes Federation (9), this prevalence is projected to double by 2045 due to high rates of abnormal glucose tolerance, including prediabetes (5, 10–12). Prediabetes and diabetes represent a glycemic continuum with both associated with vascular complications and an increased burden on all-cause mortality rates. Presently, 179.2 million individuals globally with undiagnosed diabetes (13), with the IDF Africa Region standing out with the highest rate of undiagnosed cases among all IDF regions, at 60% (14). This underscores the critical need for increased awareness, early detection, and intervention strategies to address undiagnosed diabetes in Africa.

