Due to the demographic characteristics and nature of diabetes, the biopsychosocial model of disease development underpins the CarMeR Study. The model as utilized in a previous study, propounds that disease occurrence results from the interplay of biological, psychological and social factors (37). It explains how factors, including biological factors (family history diabetes, sex), sociological factors (familial, occupation, economic status, nutrition, ethnicity, place of birth and early life experiences), and psychological factors (stress and sleep patterns) contribute to disease development. The biopsychosocial model suggests that each of these three domains has an influence on health. The biopsychosocial model has been selected because it provides a framework for understanding risk factors associated with CMDs in Ghana. As illustrated in **Figure 1**, we hypothesize that genetic factors, social factors, familial factors, stress, economic status, religion, ethnicity, nutrition patterns, physical activity and other population characteristics play a crucial role in determining an individual’s susceptibility to CMDs. Incorporating these factors into our conceptual model, we envisage gaining a deeper understanding of the complex interactions that contribute to the risks of CMDs such as diabetes, obesity, hypertension, and other cardiovascular diseases. This model will explore the prevalence of undiagnosed diabetes, prediabetes and hypertension among critical populations in Ghana, and how various factors predispose individuals to risk of cardiometabolic diseases.

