**Figure 1 f1:**
[figure not shown]
A conceptual framework for the CarMeR Study.

This project, dubbed the Cardiometabolic Risks (CarMeR) Study, is by the Bill and Melinda Gates Foundation through the African Postdoctoral Initiative, managed by the African Academy of Sciences. The objectives are: 1. determine the prevalence of undiagnosed diabetes, prediabetes and other associated cardiovascular disease risks using the multi-sampled oral glucose tolerance test [OGTT] with 82.5g monohydrate dextrose, 2. characterize the phenotype of diabetes and prediabetes relative to body composition, body mass index (BMI), and other anthropometric measures, 3. establish the ocular characteristics and complications in people with diabetes and prediabetes, 4. ascertain whether the etiology of undiagnosed diabetes is predominantly insulin resistance or beta-cell insufficiency using homeostasis model analysis of beta [HOMA-β and HOMA-IR], 5. determine the sensitivity of diagnostic alternatives to the multi-sampled OGTT, specifically the fasting plasma glucose (FPG) test and the glycated hemoglobin (HbA1c) test, and 6. determine, over a 1-year period, if changes in food choices, physical activity, weight loss and psychosocial counseling influence reversal or prevention among people newly diagnosed with diabetes and prediabetes.

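### Excluding cholesterol-medicine users from the baseline survey is justified as control of confounding, but a prevalence has nothing to confound, and the rule removes treated lipid risk from objective 1

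*Protocol article*

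**What the plan says.** All references are to the protocol article.

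- **Objectives (end of the Introduction).** Objective 1 is to "determine the prevalence of undiagnosed diabetes, prediabetes and other associated cardiovascular disease risks using the multi-sampled oral glucose tolerance test". Objective 2 is to "characterize the phenotype of diabetes and prediabetes relative to body composition, body mass index (BMI), and other anthropometric measures".
- **Population.** The target is adults aged 25 to 70 in households of the Cape Coast metropolis.
- **Exclusion criteria.** Besides pregnancy, breastfeeding and known diabetes, "those with a BMI below 18.5 kg/m², individuals with anemia, and those on cholesterol medications will be excluded from the CarMeR study". The reason for the medicine rule is that the exclusion of "participants taking high cholesterol medications is a measure taken to address the potential confounding impact of elevated cholesterol levels on diabetes prevalence". The BMI floor gets no reason of its own, only the closing general statement about participant well-being and accuracy of findings.
- **Participants.** The plan is to "recruit 1200 self-identified healthy individuals from 13 urban and rural communities in the Cape Coast Metropolis", and the same sentence adds that they have no earlier diagnosis of diabetes or prediabetes. The Inclusion criteria repeat the no-diagnosis rule but contain no test of self-perceived health.
- **Fasting blood collection and processing.** A lipid panel (cholesterol, HDL, LDL, triglycerides) is measured at baseline.
- **Data analysis.** Prevalence is to be reported as percentages with confidence intervals.

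No section limits the prevalence conclusions to the group left after these exclusions.

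**The concern.** Confounding distorts a comparison between exposed and unexposed people. The prevalence analysis is a single proportion with an interval, so there is no comparison to protect. Removing people because they carry a related risk factor does not clean a prevalence. It changes the population to which the prevalence refers.

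The rule also fails on its own terms. It selects on treatment, not on cholesterol. Someone with untreated raised cholesterol is eligible; someone whose raised cholesterol has been recognised and treated is not. Those removed belong to the group that a survey of cardiovascular risk should count.

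At stake is the lipid part of objective 1: the reported figure would describe adults not on cholesterol medicine but be read as describing all metropolis adults aged 25 to 70. A larger sample does not cure this. Two smaller matters sit alongside it. The Participants section describes recruits by self-perceived health, which the formal criteria do not contain. The BMI floor removes underweight adults from a study whose second objective is a BMI phenotype.

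**Working it through.** The plan gives no figure for the share excluded, so there is no stated result to reproduce. The sample-size figure does not bear on this point. What follows shows direction and plausible size under assumptions.

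**Formula.** Let f be the share of the target population excluded, p_in the prevalence among those included and p_ex the prevalence among those excluded.

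- True prevalence = (1 - f) × p_in + f × p_ex
- The study reports p_in, so bias = p_in - true = -f × (p_ex - p_in)

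**1. Lipid risk.** Assumptions: 1-10% of adults take cholesterol medicine, 60-100% of them count as having the risk, and 15-35% of those included have it.

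| f | p_in | p_ex | True prevalence | Understatement |
|---|---|---|---|---|
| 1% | 35% | 60% | 0.99 × 35 + 0.01 × 60 = 35.25% | 0.25 points |
| 3% | 25% | 100% | 0.97 × 25 + 0.03 × 100 = 27.25% | 2.25 points |
| 5% | 25% | 100% | 0.95 × 25 + 0.05 × 100 = 28.75% | 3.75 points |
| 10% | 15% | 100% | 0.90 × 15 + 0.10 × 100 = 23.5% | 8.5 points |

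The sign is fixed whenever p_ex exceeds p_in, which holds if treated people are counted as having the risk factor. For scale, the 95% half-width at 25% with n = 1200 is 1.96 × √(0.25 × 0.75 / 1200) = 2.45 points under simple random sampling.

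**2. Undiagnosed diabetes.** Assumptions: f = 2-10%, p_in = 6.5-10%, and relative prevalence RR in the excluded of 0.5 to 2. With p_ex = RR × p_in, bias = p_in × f × (1 - RR).

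- f = 2%, p_in = 6.5%, RR = 2: 6.5 × 0.02 × (-1) = -0.13 points
- f = 10%, p_in = 10%, RR = 2: 10 × 0.10 × (-1) = -1.0 points
- f = 10%, p_in = 10%, RR = 0.5: 10 × 0.10 × 0.5 = +0.5 points

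The simple-random-sampling half-width at n = 1200 is 1.96 × √(0.065 × 0.935 / 1200) = 1.4 points at 6.5%, and 1.96 × √(0.10 × 0.90 / 1200) = 1.7 points at 10%. The bias lies inside that margin, and its sign is not determined.

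**3. BMI floor.** Underweight people cannot be obese, so removing a share f raises observed obesity to true / (1 - f). With the plan's 17% as the true value and an assumed 2-10% underweight: 17 / 0.98 = 17.3% and 17 / 0.90 = 18.9%. The Diagnoses section defines generalised obesity as BMI of 30 or more, so the non-obese band from 18.5 to 29.9 stays fully eligible.

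**The case against.** **Lipid prevalence is not named as an endpoint.** The Introduction lists obesity, hypertension and diabetes as the cardiometabolic risk factors. Diagnoses gives no lipid cut-off. The prevalence sentence in Data analysis names only the glucose tests as its data. This stands in part, and is why the point is put as any lipid-risk prevalence. Objective 1 is nonetheless open-ended about other cardiovascular risks, and a full lipid panel is taken.

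**The diabetes effect may be nil.** Medicine users are in contact with care, so some of their diabetes may already be diagnosed and excluded anyway. This stands. A reader might infer that undiagnosed diabetes is biased downwards; the range above does not support a sign.

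**Self-perceived health is a description, not a criterion.** This also stands. A reader might infer a large loss of hypertension: if 30% are hypertensive and the half who know it all stay away, the study would report (30 - 15) / (100 - 15) = 17.6%. That is a worst case. It assumes that every aware person stays out because of an adjective that no criterion enforces, and the formal criteria do not exclude hypertension.

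**The BMI floor does not defeat the motivation.** A reader might infer that the study cuts off the lean group it was built to examine. The Introduction's premise is that African-born people "diagnosed with abnormal glucose tolerance are more likely to be non-obese", which is not a statement about underweight, and the contrast between obese and non-obese remains. Only the underweight tail is lost, and a specific reason for the floor may stand in the full protocol, which is not shown.

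None of this rescues the reason given for the medicine rule. If the worry is risk-factor associations, recording the medicine allows adjustment without narrowing the survey.

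**Conclusion.** The point holds for the cholesterol-medicine exclusion as applied to the baseline survey. Its stated reason is unsound, and the rule removes treated lipid risk while keeping untreated raised cholesterol. Any lipid-risk prevalence is understated for metropolis adults aged 25 to 70, by about 0.25 to 8.5 points. That range is illustrative: it depends on the assumed share treated and on counting treated people as affected.

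For undiagnosed diabetes the effect is probably small and of uncertain sign. The self-identified-healthy wording is an inconsistency between sections, not a demonstrated bias. The BMI floor limits what the prevalence and phenotype results describe, and no section says so. Excluding known diabetes is proper for an undiagnosed prevalence and is not in question.

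**What to change.** For the survey phase:

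1. Delete the cholesterol-medicine exclusion and its confounding rationale. Record the medicine, count users as having the lipid risk factor, and flag their lipid values as treated in analyses of measured lipids.
2. Remove the self-identified-healthy wording under Participants. That section and the Inclusion criteria already state the intended rule of no previous diagnosis of diabetes or prediabetes.
3. Either drop the BMI floor of 18.5 for the survey, or state that the prevalence and BMI-phenotype results exclude underweight adults.

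The medicine and BMI restrictions can stay as entry conditions for the lifestyle phase if wanted. The pregnancy, breastfeeding and anemia exclusions are untouched.

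If recruitment is too far advanced, tally the people excluded for each reason, and state that the prevalences apply to adults with BMI of at least 18.5 not on cholesterol medicines, not to the metropolis.

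The cost is eligibility wording and one medicine question, with the same sample size and procedures. The one small downside is that some lipid values will reflect treatment, which the flag handles. The fallback costs a screening tally and reworded conclusions.
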